### **c. Sampling**

c.1 We will conduct sampling in two stages, first selecting the health facilities and then sampling 1 of each provider type within facility; this will yield three samples (doctors, midwives, and nurses) of independent and identically distributed observations. In stage 1, we will sample from the 208 primary facilities (I3 and I4) with probability proportionate to facility distribution by tier. We will confirm that the final sample includes facilities with INFORHUS and those without. Separately, we will select two general hospitals.

In the second stage, we will request from the Ministry of Health the list of all health providers working at each health facility as well as the monthly schedule of work with basic information regarding health care worker type of contract, length working at the establishment, and similar details typically found in the National Registry of Health Personnel (INFORHUS) database. INFORHUS is an online registry in which all

institutions in the health sector must record detailed information about their employees regardless of position and type of contract. Within each sampled facility, we will confirm the schedule for the coming week with the facility manager or obtain a schedule for the week for those facilities not covered by INFORHUS. We will randomly sample two shifts from this schedule, the first as the intended observation and the second as a replacement in case a provider declines to participate, and will sample one provider of each type within the selected shifts.

We calculate sample size sufficient to provide a confidence interval of width  $\pm 3\%$  around the primary outcome of time spent on direct patient care. Drawing from existing literature on time-motion observations, we estimate standard deviation in this outcome up to 10%, which results in a sample of 54 providers per tier at primary care level. The table below shows expected distribution of health facility types in the final sample.

| Área               | Category | Total | Sample |
|--------------------|----------|-------|--------|
| Lima Metropolitana | I-3      | 176   | 35     |
|                    | I-4      | 32    | 19     |
|                    | II y II  | 24    | 2      |
| TOTAL              |          | 232   | 56     |

Note that we will sample 5 providers of each type within the hospitals for a total sample of 56 facilities and 192 observations.

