## 22 23 **f. Data analysis and report**

### 24 **f.1 Provider skill assessment**

25 Provider self-assessment of skills and identification of necessary skills will be summarized  
26 using descriptive statistics overall, within tier of facility, and within provider cadre.  
27 Differences between groups will be tested using the Kruskal-Wallis test for equality of  
28 distributions or Chi squared test for differences in proportions based on the selected  
29 variable type. Analysis will seek to identify the most important skills providers selected,  
30 the current capacity of providers in these areas, and any differences between  
31 perspectives based on cadre, facility tier, or other salient provider characteristics. Health  
32 facility directors will be classified as a unique group to enable consideration of their  
33 perspectives. Predictors of identification of specific skills can be assessed with  
34 multivariable regression as appropriate.

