### 35 36 **f.2 Time and motion study**

37 Time spent per task will be summarized using descriptive statistics (e.g. mean, median,  
38 interquartile range); task predominance will be ranked within sub-groups. Outlying  
39 providers and facilities will be identified using data visualizations as well as descriptive  
40 statistics. Differences between groups such as facility tier and provider cadre will be  
41 tested using the Kruskal-Wallis test for equality of distributions or t-tests as appropriate,  
42 with multivariate regression (generalized estimating equation models to account for  
43 repeated sampling within facilities) applied as needed to control for individual covariates  
44 in identifying determinants of time use.

1 The final report will provide visual and quantitative descriptive results from both  
2 instruments.

3  
4 **Ethical Aspects**

5 The protocol and instruments will be presented for review and approval to the ethics  
6 committee of the Universidad Peruana Cayetano Heredia. The study will be discussed  
7 with the Ministry of Health authorities to get their support to avoid having to go through  
8 each health establishment ethics approval. We will ask for an exception of approval for  
9 the first observation but will require inform consent for the direct observation of the  
10 provider by the director of the center and by the provider itself. We will require a separate  
11 consent for the skills survey.  
12  
13

1 STROBE Statement—Checklist of items that should be included in reports of *cross-sectional studies*

| STROBE Statement – Checklist of items that should be included in reports of cross-sectional studies |         |                                                                                                                                                                                                              | Page No |
|-----------------------------------------------------------------------------------------------------|---------|--------------------------------------------------------------------------------------------------------------------------------------------------------------------------------------------------------------|---------|

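### The stated group tests ignore that providers share a facility: cadre tests become conservative and lose power, and tier tests reject too often when cadres are pooled or hospitals form a tier

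*Combined protocol and SAP*

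**What the plan says.** On time use, f.2 states: "Differences between groups such as facility tier and provider cadre will be" "tested using the Kruskal-Wallis test for equality of distributions or t-tests as appropriate". The same sentence continues "with multivariate regression (generalized estimating equation models to account for" "repeated sampling within facilities) applied as needed to control for individual covariates". GEE is therefore available, but its use is conditional and tied to covariate adjustment.

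On skills, f.1 states: "Differences between groups will be tested using the Kruskal-Wallis test for equality of" distributions, or a Chi squared test for proportions. It mentions multivariable regression for predictors and no method for clustering.

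On the sample, section c. Sampling describes "sampling 1 of each provider type within facility; this will yield three samples (doctors, midwives, and nurses) of independent and identically distributed observations". Its table gives 35 of 176 I-3 facilities and 19 of 32 I-4 facilities. Two hospitals, selected separately, supply 5 providers of each type, and the total is 56 facilities and 192 observations. One provider of each type is drawn within the selected shifts.

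The plan does not say whether tier is tested within each cadre or over all cadres together, or whether hospitals count as a tier in the tests. It gives no significance level and no ICC.

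**The concern.** Cadre varies within a facility and tier varies between facilities. If colleagues at one facility resemble each other in how they spend time, through shared patient load, records system or shift, an independent-samples test uses the wrong variance in both comparisons, and the two errors run in opposite directions.

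For cadre, the three samples are matched by facility. Ignoring the match overstates the variance of the difference, so real cadre differences are missed more often than they need be. This holds however the plan is read, because a cadre comparison has to set the three samples against each other.

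For tier, pooling three colleagues per facility, or 15 per hospital, understates the variance, so tier differences can be declared where there are none. Whether this happens depends on choices that the plan leaves open.

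**Working it through.** **1. The plan's own figures.** Inputs from c. Sampling: SD 10 points, half-width 3 points; 95% confidence is assumed. n0 = (1.96 × 10 / 3)² = 42.7. With a finite population correction by tier, n0 / (1 + (n0 − 1)/N) gives 34.5, so 35, for N = 176, and 18.5, so 19, for N = 32. The sum is 54, as in the table, and 54 × 3 + 2 × 15 = 192, as stated. So 54 is the number per cadre over both primary tiers, although the text calls it a number per tier; that wording should be reconciled.

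**2. Formulas for primary care** (two-sided 5%, assumed; ICC = ρ, assumed).

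- Pooled I-3 versus I-4 (105 versus 57 providers): with 3 per facility the true variance is (1 + 2ρ) times the naive one. Rejection of a true null = 2[1 − Φ(1.96/√(1 + 2ρ))]. At ρ = 0.2: 1.96/√1.4 = 1.66, giving 9.8%. The effective size of 162 providers is 162/1.4 = 116.
- Two cadres over 54 facilities: the true variance of the difference is (1 − ρ) times the naive one. Rejection = 2[1 − Φ(1.96/√(1 − ρ))]. At ρ = 0.2: 1.96/√0.8 = 2.19, giving 2.8%.
- I-3 versus I-4 within one cadre: one provider per facility, so the design effect is 1.

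**3. Simulation** (normal data, SD 10, facility random effect, 35 + 19 facilities of 3 and, where named, 2 hospitals of 15; 20,000 samples per ICC). Rejection of a true null, in percent:

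| Test | ICC 0.05 | 0.1 | 0.2 | 0.3 |
|---|---|---|---|---|
| I-3 vs I-4, pooled over cadres, formula | 6.2 | 7.4 | 9.8 | 12.1 |
| Same, Kruskal-Wallis, simulated | 6.1 | 7.3 | 9.5 | 11.9 |
| I-3 vs I-4 within one cadre, t-test | 4.9 | 5.1 | 4.7 | 4.9 |
| I-3 vs I-4 on facility means, t-test | 5.0 | 5.1 | 4.9 | 5.0 |
| Three tiers with hospitals, pooled, Kruskal-Wallis | 10.9 | 16.8 | 27.3 | 36.4 |
| Three tiers with hospitals, within cadre, Kruskal-Wallis | 6.1 | 7.3 | 10.0 | 13.3 |
| Three cadres, Kruskal-Wallis | 4.4 | 3.6 | 2.4 | 1.4 |
| Three cadres, facility as block | 5.1 | 5.0 | 5.0 | 4.9 |

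At ICC 0 all of these are close to 5%. Repeats with other seeds agree: pooled I-3 versus I-4 5.7% to 12.9%, three tiers pooled 10.0% to 36.8%, cadre 4.4% to 1.4%.

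**4. Cadre power.** For one cadre shifted by an assumed 4 points at ICC 0.2: about 53% with Kruskal-Wallis and 66% with facility as a block. For an assumed 5-point shift at ICC 0.05 / 0.1 / 0.2 / 0.3: 74 / 74 / 75 / 75% against 78 / 80 / 85 / 89%. A Friedman test, the usual rank test for blocks, reaches only 52% for the 4-point shift at ICC 0.2, so it does not recover the gain.

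No figures were computed for the f.1 skill items. The same providers are compared there, so the directions carry over, but the sizes need not.

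**The case against.** - **The plan saw the clustering.** GEE stands in the same sentence of f.2, with that purpose. This stands in part: the tool is named, but an analyst following the text could report every group test without it, and f.1 has no counterpart.
- **The independence statement is correct.** A reader might infer that c. Sampling wrongly calls the whole data set independent. It does not: it speaks of three samples, one per cadre, and among primary facilities each such sample has one provider per facility. It fails only between cadres and for the hospitals, with 5 per cadre at each site.
- **Tier tests need not be inflated.** A reader might infer that every tier test rejects too often. The documents do not support that: within one cadre, I-3 versus I-4 holds its level at every ICC tried, and nothing says tier is tested pooled. This stands, and the tier part of the point is conditional on it.
- **The largest figures need a test that the plan does not spell out.** The 10% to 37% arises only if two separately selected hospitals are tested as a pooled third tier. This also stands.
- **Finite population.** If inference is confined to the 208 primary facilities, of which 19 of 32 I-4 sites are sampled, pooled I-3 versus I-4 rejection falls to 5.2 / 5.8 / 6.7 / 6.9% at ICC 0.05 / 0.1 / 0.2 / 0.3. This stands for that target; the plan does not state which target the tests address.
- **The cadre error is on the safe side.** It creates no false findings, and power does not fall below that of independent samples. True; the loss is relative to what the same data could give.
- **The study is mainly descriptive,** sized for a confidence interval. The single-cadre means in primary care, which that sizing concerns, are unaffected. Group differences are nonetheless the stated inferential content of f.1 and f.2.
- **The STROBE checklist** cites manuscript pages for methods that account for the sampling. Those pages are not among the documents and cannot be weighed.

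**Conclusion.** The point holds in a bounded form. The cadre tests ignore facility matching on any reading: for positive ICC they are conservative, at about 4% to 1.5%, and give up about 13 percentage points of power (53% against 66%) for a 4-point shift at ICC 0.2. Tier tests are anti-conservative only when pooled over cadres (I-3 versus I-4, about 6% to 13%, less under a finite-population target) or when the hospitals form a tier (about 10% to 37% pooled, 6% to 13% within cadre). Within-cadre I-3 versus I-4 tests in primary care are sound.

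These sizes rest on an assumed ICC of 0.05 to 0.3, a common SD of 10 points, normal data and a 5% level. With no correlation within facilities the problem disappears, but a shared site and shift make zero hard to presume.

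**What to change.** In both f.1 and f.2, make the cluster-aware analysis the default and remove the as-needed condition.

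- **Cadre:** a linear mixed model with a facility random intercept, or the GEE already named, with cadre as a factor, over the 54 primary facilities. For binary skill items use the logistic mixed model or the GEE equivalent. Do not substitute Friedman: it loses the power gain and needs complete blocks, and Table S3 shows unequal cadre totals (57, 59 and 56).
- **Tier:** test I-3 versus I-4 within cadre, where Kruskal-Wallis and t-tests may stay, or on facility means.
- **Hospitals:** report descriptively and not as a tested tier; two sites give almost no between-facility replication.
- **c. Sampling:** state that the independence description applies within one cadre among primary facilities only.

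The cost is analysis wording; no further data are needed. Any tier comparison that would have been pooled will give less favourable p-values, and hospitals can no longer be claimed to differ on the strength of a test.

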| ACTIVIDAD     |                                                                                                                                                                                                                                         |                                                                                                                                                                           |                                                                                                                                                 |
|---------------|-----------------------------------------------------------------------------------------------------------------------------------------------------------------------------------------------------------------------------------------|---------------------------------------------------------------------------------------------------------------------------------------------------------------------------|-------------------------------------------------------------------------------------------------------------------------------------------------|
| Categoría     | PC-Lee                                                                                                                                                                                                                                  | PC-escribe                                                                                                                                                                | Personal                                                                                                                                        |
| Subcategorías | Registros
Archivos administrativos
Recetas
Historia clínica
Resultados laboratorio
Motor búsqueda
Correo electrónico
Personal
Otros                                                                             | Historia clínica electrónica

Transcribir HCE
Transcribe otros
Registro directo
CNV
Otros                                                               | Marcar asistencia

Comer
Dormir
Tiempo ocioso
Higiene
Baño
Otro                                                            |

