| Categoría     | Pape-lee                                                                                                                                                                                                                                | Papel-escribe                                                                                                                                                             | Desplazamiento                                                                                                                                  |
| Subcategorías | Historia clínica
Carnets
Exámenes auxiliares

Registro citas
Registros - otros
Referencias (libros u otros)
Otros                                                                                                  | Historia clínica
Carnets
Citas

Referencia/interconsulta
FUA/HIS

Receta
Solicita pruebas
Altas
Registros-otros
Lista de chequeo
Otro | Traslado del paciente
Dentro del EESS
Fuera del EESS
Fuera del EESS - Visita domiciliaria
Otro                                      |
| Categoría     | Procedimientos                                                                                                                                                                                                                          | Búsqueda                                                                                                                                                                  | Otro                                                                                                                                            |
| Subcategorías | Examen físico/signos
Tamizajes
Entrega alim/suplem/medic
Administración medicamentos
Electrocardiograma
Curación heridas
Pruebas rápidas
Atención de partos
Estimulación
Rehabilitación
Ecografía
Otro | Preparación de materiales e insumos
Profesional de salud

Personal técnico

Personal administrativo
Paciente
Historia clínica
Otro                | Inactividad
Pausa del observador

Observador no en el cuarto

No identificados
Otro                                           |

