| Categoría | PC-Lee                                                                                                                                                                                                                            | PC-escribe                                                                                                                                                         | Personal                                                                                                          |
| Subcategorías    | Registros
Archivos administrativos
Recetas
Historia clínica
Resultados laboratorio
Motor búsqueda
Correo electrónico
Personal
Otros                                                                              | Historia clínica electrónica
Transcribir HCE
Transcribe otros
Registro directo
CNV
Otros                                                                   | Marcar asistencia
Comer
Dormir
Tiempo ocioso
Higiene
Baño
Otro                                         |
| Categoría | Pape-lee                                                                                                                                                                                                                          | Papel-escribe                                                                                                                                                      | Desplazamiento                                                                                                    |
| Subcategorías    | Historia clínica
Carnets
Exámenes auxiliares

Registro citas
Registros - otros
Referencias (libros u otros)
Otros                                                                                                   | Historia clínica
Carnets
Citas

Referencia/interconsulta
FUA/HIS

Receta
Solicita pruebas
Altas
Registros-otros
Lista de chequeo
Otro | Traslado del paciente
Dentro del EESS
Fuera del EESS
Fuera del EESS - Visita domiciliaria
Otro               |

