| Documentation   | Doc: paper                  | 11.4%                      | 9.5%                    | 18.5%                      | 11.2%                   | 18.8%                      | 7.1%                    |
|                 | Doc: PC                     | 1.6%                       | 0.6%                    | 3.5%                       | 1.3%                    | 5.7%                       | 8.3%                    |
| Communication   | Comm consults: paper        | 3.1%                       | 0.4%                    | 0.0%                       | 0.1%                    | 0.9%                       | 0.3%                    |
|                 | Comm consults: PC           | 0.1%                       |                         |                            |                         | 0.1%                       |                         |
|                 | Prof communication: other   | 4.9%                       | 6.9%                    | 11.9%                      | 8.6%                    | 6.5%                       | 9.6%                    |
|                 | Communication: other        | 3.1%                       | 7.2%                    | 1.8%                       | 3.5%                    | 1.4%                       | 3.7%                    |
| Administrative  | Admin: FUA                  | 10.7%                      | 2.4%                    | 3.5%                       | 0.3%                    | 8.1%                       | 2.0%                    |
|                 | Other admin                 | 0.1%                       |                         | 0.0%                       |                         | 0.4%                       | 1.1%                    |
| Transit         | Transit                     | 10.4%                      | 4.6%                    | 10.4%                      | 10.0%                   | 6.6%                       | 17.9%                   |
| Education       | Education                   | 1.8%                       | 0.0%                    | 0.3%                       |                         | 0.4%                       | 0.2%                    |
| Personal/social | Personal: eat/sleep/hygiene | 2.8%                       | 20.3%                   | 3.3%                       | 8.2%                    | 3.7%                       | 9.2%                    |

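### FUA forms, prescriptions and several other writing tasks have a code on paper but none on computer, so the documentation contrast by computer use in Table S5 may partly reflect the medium

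*Combined protocol and SAP*

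**What the plan says.** Figure S1 (doctors) and Figure S2 (nurses and midwives) list the activity codes.

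- **Writing on paper (Papel-escribe).** Both figures include the run "Referencia/interconsulta FUA/HIS Receta Solicita pruebas Altas Registros-otros Lista de chequeo Otro". Appointments (Citas) have a code earlier in the same list.
- **Writing on computer (PC-escribe).** After the electronic record itself, the rest of the list, the same in both figures, is "Transcribir HCE Transcribe otros Registro directo CNV Otros".
- **Reading on computer (PC-Lee).** This list includes "Archivos administrativos Recetas", so prescriptions and administrative files on a computer were foreseen, but only as something read.

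Table S4 reports FUA under Administrative and Medication as its own type, neither with a paper/PC split. Documentation is split by medium, and so are consults: "Comm consults: paper" and "Comm consults: PC" both sit under Communication. Table S5 compares documentation between computer users and non-users within each cadre. Section f.2 plans to rank tasks within sub-groups and to compare groups. No section gives the rule that turns observation codes into the activity types of Table S4.

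**The concern.** If a task has its own code on paper and none on computer, an observer who sees it typed has to use a general code such as Registro directo, Transcribe otros or Otros. If general PC writing is then counted as documentation, a provider who moves a form from paper to computer appears to do more documentation and less administration, although the work is the same. Table S5 makes exactly the contrast on which the code list is not neutral. A reader could not tell whether computer users document more or whether some of their tasks were relabelled.

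**Working it through.** **1. Code coverage for writing, Figures S1 and S2 against Table S4**

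| Task | Paper code | PC code | Place in Table S4 | Change of type with medium |
|---|---|---|---|---|
| FUA/HIS form | yes | no | Admin: FUA, no split by medium | possible, see step 2 |
| Prescription | yes | no | not named; Medication is an assumption | possible under that assumption |
| Referral/consult | yes | no | consult rows for paper and PC, same type | not shown |
| Test order, appointment, discharge | yes | no | no named row | cannot be judged |
| CNV | no | yes | no named row | the reverse asymmetry |

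**2. Does Table S5 documentation include FUA?** Weight the Table S4 rows by shift N (outpatient, hospital), pool Table S5 over users and non-users, and compare.

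Doc: paper + Doc: PC from Table S4:
- Doctors: (49 × 13.0 + 7 × 10.1)/56 = 12.6%
- Nurses: (46 × 22.0 + 5 × 12.5)/51 = 21.1%
- Midwives: (46 × 24.5 + 8 × 15.4)/54 = 23.2%

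Documentation from Table S5, with the range that rounding allows:
- Doctors: (35 × 12 + 19 × 15)/54 = 13.1% (12.6 to 13.6)
- Nurses: (30 × 19 + 27 × 20)/57 = 19.5% (19.0 to 20.0)
- Midwives: (14 × 14 + 42 × 26)/56 = 23.0% (22.5 to 23.5)

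Doctors and midwives agree within rounding; nurses do not. Adding the FUA row raises the Table S4 figures to 22.3%, 24.3% and 30.3%. That fits no cadre and makes the nurse mismatch worse. Table S5 documentation therefore appears to leave FUA out.

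**3. Upper bound on the artefact.** Suppose that misplaced typed tasks sit in Doc: PC. They cannot exceed that row. Weighted Doc: PC is:
- Doctors: (49 × 1.6 + 7 × 0.6)/56 = 1.48 points
- Nurses: (46 × 3.5 + 5 × 1.3)/51 = 3.28 points
- Midwives: (46 × 5.7 + 8 × 8.3)/54 = 6.09 points

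If all of it falls among the Table S5 computer users, divide by the user fraction:
- Doctors: 1.48/(19/54) = 4.2 points
- Nurses: 3.28/(27/57) = 6.9 points
- Midwives: 6.09/(42/56) = 8.1 points

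**4. Against the Table S5 gaps.** User minus non-user difference, with SE = √(s₀²/n₀ + s₁²/n₁) and a normal-approximation 95% interval:

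| Cadre | Gap (points) | 95% CI | Bound (points) |
|---|---|---|---|
| Doctors | 15 − 12 = +3 | −1.3 to 7.3 | 4.2 |
| Nurses | 20 − 19 = +1 | −6.3 to 8.3 | 6.9 |
| Midwives | 26 − 14 = +12 | 6.6 to 17.4 | 8.1 |

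The bound exceeds the doctor and nurse gaps. For midwives it is 8.1/12, about two thirds of the gap.

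**The case against.** A reader might infer that every one of these tasks changes activity type once typed, and that documentation is overstated wherever computers are used. The documents do not support that, for these reasons.

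- **The mapping is not given.** Nothing says where the generic PC codes went, or whether Otros entries were recoded. The STROBE checklist points to manuscript pages for variables and measurement that are not part of these documents.
- **Referrals point the other way.** Table S4 has a PC row for consults in the same type as the paper row, so not all PC work went to Doc: PC. No PC writing code names that task, so the source of the row is unexplained.
- **The FUA row is not proof by itself.** It carries no medium label and could pool both media.
- **Nothing shows how often these tasks were typed.** The prescription code on computer is for reading. The lists may simply reflect the medium in use, and a pilot with revision of the tools was planned. If FUA was always on paper and prescriptions were always handwritten, the effect is zero.
- **The bound is loose.** Doc: PC presumably also holds genuine electronic-record writing. Tables S4 and S5 cover different samples (56, 51 and 54 providers against 54, 57 and 56).
- **The comparison is secondary.** Section f.2 does not plan a contrast by computer use, and Table S5 is a supplementary descriptive table.

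All of this stands, and it limits the point to a possible artefact. It does not remove it. The codes differ by medium in both figures, a typed FUA form has no code of its own, and the reported contrast is by computer use.

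**Conclusion.** The point holds as a possible, bounded artefact. The asymmetry in the writing codes is printed in both figures. A change of activity type is well supported as a possibility for FUA, conditional for prescriptions on Receta feeding Medication, not shown for referrals, and not assessable for test orders, appointments or discharges. CNV runs in the opposite direction.

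If FUA forms or prescriptions were typed and generic PC writing was counted as Doc: PC, Table S5 may overstate documentation among computer users, and administration may be understated. The effect lies between zero and roughly 4, 7 and 8 points for doctors, nurses and midwives. These bounds assume that all PC documentation falls among Table S5 users. The nurse figure is the least secure, because nurse documentation does not reconcile between the two tables. The artefact could cover the doctor and nurse gaps, whose intervals include zero in any case, but it cannot account for the whole midwife gap. The primary outcome in the sampling section (c.1), time on direct patient care, is not affected.

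**What to change.** For any further fieldwork, give PC-escribe the same purpose codes as Papel-escribe (FUA/HIS, prescription, referral, test order, appointment, discharge) and map both media to the same activity type. The cost is a slightly longer tablet menu for observers.

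For the data already collected:

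1. State the mapping from observation codes to Table S4 activity types, including the three generic PC codes and the source of the PC consult row.
2. Re-map Transcribe otros, Registro directo and Otros to their purpose where the logs allow.
3. Repeat the user/non-user comparison of Table S5 on a combined writing outcome: documentation, FUA, prescriptions and consults, on paper and PC together.
4. Base any statement about computers and documentation on that combined outcome.

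This costs one extra analysis and no new data. The downside is that the combined outcome is less specific than documentation alone.
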